## Abstract

**Purpose:**

Early childhood is a critical period for both motor and neurodevelopment, yet less is known about whether behavioral improvements following motor-focused physical education are accompanied by concurrent functional neural indicators. This protocol describes a cluster-randomized trial evaluating the effects of a semester-long motor-focused exercise program on gross motor competence and exploratory neurodevelopmental outcomes in preschool children.

**Methods:**

This two-arm, cluster-randomized controlled trial will recruit approximately 110 children aged 4–6 years from kindergartens in Changsha, China. Classes will be randomized 1:1 to either an intervention group receiving structured motor-focused physical education or a control group receiving ordinary physical education. The intervention will be delivered three times weekly for 30–40 min over 16 weeks, emphasizing locomotor and object-control skills through progressive, game-based activities. The primary outcome will be gross motor competence measured by the Test of Gross Motor Development–Third Edition (TGMD-3). Secondary outcomes will include portable electroencephalography (EEG) measures of resting-state and task-related brain activity associated with inhibitory control and attentional regulation. Optional measures will include parent- and teacher-reported questionnaires of executive function and behavioral adjustment. Group-by-time effects will be analyzed using linear mixed-effects models under an intention-to-treat framework.

**Discussion:**

This trial will examine whether structured motor-focused physical education is associated with improvements in gross motor competence and concurrent functional neural indicators in preschool settings. Findings will contribute incremental evidence to the developmental literature linking motor and neurocognitive processes and may inform future research on scalable approaches to support early childhood development.

**Clinical Trial Registration:**

https://clinicaltrials.gov/study/NCT07307742 identifier NCT07307742.

## Introduction

1

Early childhood represents a critical period for pediatric neurodevelopment, during which foundational motor, cognitive, and behavioral systems undergo rapid maturation and reorganization. Between the ages of 4 and 6 years, children demonstrate substantial advances in gross motor coordination, executive control, attentional regulation, and sensorimotor integration (1, 2). These domains are routinely monitored within pediatric developmental surveillance frameworks because early weaknesses in motor competence and self-regulatory functioning have been associated with elevated risk for later academic underachievement, behavioral dysregulation, developmental coordination disorder, and attention-deficit/hyperactivity disorder (3–5). Accordingly, identifying modifiable environmental exposures that may strengthen early developmental trajectories remains an important priority in preventive pediatric research.

Gross motor competence is increasingly recognized not only as an indicator of physical capability but also as a potential marker of broader neurodevelopmental status. Children with lower motor proficiency are more likely to exhibit executive function difficulties, reduced self-regulation, and challenges in social participation (5, 6). Structured physical-activity interventions delivered in preschool settings consistently demonstrate improvements in locomotor and object-control skills, with meta-analytic evidence reporting moderate to large behavioral effects (7). Although behavioral efficacy is well established, considerably less is known about whether improvements in motor competence are accompanied by measurable changes in functional neural systems supporting executive and attentional processes. In particular, few randomized preschool trials have examined behavioral and neurophysiological outcomes within the same experimental framework.

From a developmental neuroscience perspective, motor and cognitive systems are functionally interconnected during early childhood. The cerebellum and prefrontal cortex exhibit parallel maturation patterns, and functional connectivity between motor and association networks strengthens markedly across the preschool years (1). Beyond its classical motor role, the cerebellum contributes to executive control, attentional modulation, and behavioral regulation (8). Theoretical accounts grounded in embodied cognition and dynamic systems theory further suggest that repeated, structured motor experiences may influence neural network refinement through experience-dependent processes (4, 9). Despite this theoretical foundation, experimental evidence linking structured motor training to concurrent functional neurodevelopmental indicators in typically developing preschool populations remains limited.

Beyond educational implications, motor competence occupies a recognized position within pediatric developmental monitoring frameworks, where delays in gross motor coordination and self-regulatory behaviors often prompt further evaluation for neurodevelopmental disorders (10). Understanding whether structured motor enrichment strengthens motor competence and is associated with favorable neurodevelopmental indicators therefore carries relevance for preventive pediatric practice. If scalable motor-focused programs delivered within routine kindergarten settings demonstrate measurable developmental benefits, they may represent a feasible population-level strategy to support early developmental trajectories prior to the emergence of clinically significant impairments. Furthermore, identifying functional neural correlates associated with motor enrichment may inform future research aimed at refining early risk detection models, complementing existing behavioral surveillance approaches used in pediatric care.

Therefore, the objective of the present trial is to evaluate the effects of a semester-long motor-focused physical education program on gross motor competence and exploratory neurodevelopmental indicators in preschool children. Based on existing behavioral and developmental neuroscience literature, we hypothesize that children receiving the motor-focused intervention will demonstrate greater improvements in gross motor competence than those in the control condition, exhibit changes in pre-specified electroencephalography (EEG) indices associated with inhibitory control and attentional regulation, and show positive associations between gains in motor competence and changes in functional neural indicators. By integrating standardized behavioral assessment with non-invasive measures of functional brain activity within real-world kindergarten settings, this study aims to clarify whether structured motor enrichment is accompanied by concurrent neurodevelopmental correlates during a sensitive developmental window.

## Methods and analysis

2

### Study design

2.1

This study is a prospective, two-arm, parallel-group, cluster-randomized controlled trial designed to evaluate the effects of a semester-long (approximately 16 weeks) motor-focused physical education program on gross motor competence and neurodevelopment in preschool children. The study will be conducted in kindergartens from Changsha, Hunan Province, China. The trial follows the recommendations of the SPIRIT 2025 statement for standardized protocol reporting (11). As shown in Figure 1, all participants will undergo eligibility screening, informed consent, and baseline assessments prior to randomization (week 0). The intervention phase spans 16 weeks, during which classes receive either structured motor-focused physical education or ordinary physical education. Outcome assessments are scheduled at baseline (week 0) and immediately post-intervention (week 16). This schedule ensures standardized evaluation and facilitates examination of both motor and neural effects of the intervention.

**Figure 1 F1:**
[figure not shown]
Schedule of enrolment, interventions, and assessments. TGMD-3, test of gross motor development, third edition; EEG, electroencephalography; BRIEF-P, Behavior Rating Inventory of Executive Function-Preschool Version; SDQ, Strengths and Difficulties Questionnaire.

### Participants

2.2

Children eligible for this study will be those enrolled in participating kindergartens and aged between 4 and 6 years at the time of recruitment. Participants must be physically healthy and able to engage safely in structured physical education activities. Only children whose parents or legal guardians provide written informed consent will be included.

Children will be excluded if they (1) have diagnosed neurological, developmental, or musculoskeletal disorders that may interfere with motor performance or EEG measurement; (2) are currently enrolled in specialized sports or motor-training programs outside the kindergarten curriculum; or (3) are unable to comply with EEG assessment procedures due to behavioral or sensory intolerance. Children with mild, well-managed conditions (e.g., attention deficit) will not be excluded.

Recruitment will be carried out in collaboration with kindergarten administrators and teachers. Parents will receive written and verbal information about the study objectives, procedures, and potential benefits and risks. Recruitment meetings will be held in participating school to address questions from parents and staff. Consent forms will be distributed to parents, and only children with returned signed consent will be enrolled.

### Sample size

2.3

The sample size was calculated to detect meaningful differences in gross motor competence between the intervention and control groups, while accounting for the cluster-randomized design. Previous intervention trials and meta-analyses of preschool motor-skill programs have consistently reported large effect sizes, often exceeding 1.0, for improvements in fundamental motor skills (7). Based on this evidence, we adopted an assumption of an effect size of 1.0 for between-group differences.

Using a two-tailed alpha of 0.05 and a statistical power of 80%, an individually randomized design would require approximately 21 children per group. Because this study uses class-level randomization, the required sample size was adjusted for clustering. Assuming an average class size of 25 and an intra-class correlation coefficient of 0.05, the design effect is estimated at 2.2. This adjustment results in an effective sample size of 46 children per group, or 92 children in total. To accommodate an anticipated dropout rate of 15%, we plan to recruit approximately 110 children overall, distributed across four to six kindergarten classes in Changsha city.

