### Randomization and blinding

2.4

Randomization will be performed at the class level. After baseline assessments are completed, participating classes will be randomly assigned in a 1:1 ratio to either the intervention group (motor-focused physical education) or the control group (ordinary physical education). The allocation sequence will be generated by an independent researcher using a computer-based random number generator and will not be disclosed to the assessment team until all baseline testing has concluded.

Due to the nature of the intervention, it is not possible to blind teachers or participants to group allocation. However, outcome assessors will remain blinded throughout the study. Specifically, individuals conducting the motor skill assessments and EEG recordings will not be informed of class assignments. To further reduce bias, video recordings of motor skill performances will be scored by two independent raters who are blinded to intervention status and assessment time point. Data analysts will also be blinded to group labels until the primary analyses are completed.

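### The stated inputs (effect size 1.0, two-sided 5%, 80% power) need 16 to 17 children per group, not about 21; the later sample-size steps are sound but inherit this base

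*Protocol article*

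**What the plan says.** All the inputs stand in the Sample size section (2.3) of the protocol article, except the allocation ratio.

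- Effect size: "we adopted an assumption of an effect size of 1.0 for between-group differences".
- Error rates and base number: "Using a two-tailed alpha of 0.05 and a statistical power of 80%, an individually randomized design would require approximately 21 children per group".
- Clustering: "Assuming an average class size of 25 and an intra-class correlation coefficient of 0.05, the design effect is estimated at 2.2".
- Clustered size: "This adjustment results in an effective sample size of 46 children per group, or 92 children in total".
- Dropout: "To accommodate an anticipated dropout rate of 15%, we plan to recruit approximately 110 children overall".
- Allocation, from Randomization and blinding (2.4): "participating classes will be randomly assigned in a 1:1 ratio".

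No other power, effect size, test or correction is given that would lead to 21. Dropout and clustering enter as separate steps after the base number.

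**The concern.** For a two-arm comparison of means with a standardised effect of 1.0, two-sided 5% and 80% power, the familiar answer is 16 or 17 per group. A base of 21 is too far from that for the word 'approximately' to cover. Every later figure is built on it, and this section is the only justification given for recruiting about 110 young children.

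The stake is reproducibility. A reader who repeats the calculation cannot reconcile the power and effect size with the number, and so cannot tell whether the trial is sized for 1.0 at more than 80% power or for a somewhat smaller effect at 80%. The section also calls the clustered figure of 46 'effective', a term that normally means the number after division by the design effect.

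**Working it through.** **Inputs.** d = 1.0 (SD = 1), two-sided alpha 0.05, power 80%, 1:1 allocation, class size 25, intra-class correlation 0.05, dropout 15%.

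**1. The article's own steps, starting from 21.**
- Design effect: 1 + (25 − 1) × 0.05 = 2.2. Agrees.
- Clustered size: 21 × 2.2 = 46.2, stated as 46. Agrees, rounded down.
- Total: 2 × 46 = 92. Agrees.
- Dropout: 92 / 0.85 = 108.2, stated as about 110. Agrees.

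**2. The base number from the stated inputs.**
- Normal approximation: n = 2(1.960 + 0.842)² / 1.0² = 15.70, so 16 per group.
- Exact t-test (noncentral t, df = 2n − 2, noncentrality d√(n/2)): n = 16 gives 78.1% power and n = 17 gives 80.7%, so 17 per group.
- Stated: 21. Excess: 21/17 = 1.24 and 21/16 = 1.31, that is 24% to 31%.

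**3. What 21 per group delivers at d = 1.0.**
- Normal: Φ(√(21/2) − 1.960) = Φ(1.280) = 90.0%.
- t-test: 88.5%.
- After clustering: 46 / 2.2 = 20.9 effective children per group, which gives 88.4% (t-test) to 89.9% (normal).

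**4. Which other inputs could produce 21?** Each row changes one input.

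| Change | Per group |
|---|---|
| One-sided alpha 0.05 | 13–14 |
| 85% power | 18–19 |
| Wilcoxon efficiency loss | 18–20 |
| 15% dropout already in the base | 19–20 |
| 90% power, normal | 21.01 (22 if rounded up) |
| 90% power, t-test | 23 |
| 80% power, d = 0.89 or 0.90, t-test | 21 |
| 80% power, two-sided alpha 0.025, t-test | 21 |

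More than one route reaches 21, and the article states none of them.

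**5. What the stated inputs lead to.**
- From 17: 17 × 2.2 = 37.4, so 38 per group; 76 in total; 76 / 0.85 = 89.4, so about 90.
- From 16: 16 × 2.2 = 35.2, so 36 per group; 72 in total; 72 / 0.85 = 84.7, so 85.
- The stated target of about 110 is therefore some 20 to 25 children above what the stated inputs require. About 2 of these come from rounding 108 up to 110.

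**The case against.** The strongest reply is that the slip does no harm. On the article's own design-effect method the planned size exceeds the stated 80% power, the effect of 1.0 is clearly stated, and the Discussion again describes the trial as powered for large effects. Both 90 and 110 children fit the planned four to six classes (90/25 = 3.6 and 110/25 = 4.4). This stands: the slip changes neither recruitment nor design nor analysis. It does not make 21 follow from the stated inputs, and a fuller protocol or analysis plan could not do so either.

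The documents do not support four stronger readings.

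- *The authors used 90% power.* A reader might infer this from 21.01, but the t-test needs 23 at 90% power, and a slightly smaller effect at 80% power also gives 21. The source is unknown.
- *The whole chain is wrong.* Only the base fails; each later step checks.
- *Calling 46 'effective' claims twice the information the trial has.* The sentence follows directly from 21 and the design effect, and 46 is then inflated for dropout as a head count. The term is loose, and correcting it is editorial.
- *The trial is oversized and could recruit fewer children.* The calculation takes no account of the few degrees of freedom that four to six classes provide (classes minus 2, so 2 to 4 in a class-level comparison). That is a separate issue, but it rules out treating the difference as spare.

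**Conclusion.** The concern holds in a limited form. As written, the base of about 21 per group is wrong for d = 1.0, two-sided 5% and 80% power: the requirement is 16 (normal) or 17 (t-test). At least one of the stated power, the stated effect size and the base number must change. The figures 46, 92 and about 110 are correctly derived from 21 and are high only because 21 is.

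The direction is conservative: about 88% to 90% power at d = 1.0 instead of 80%. This assumes the article's own method, namely a two-sample comparison of means with design effect 2.2 and no allowance for the small number of classes. It is not a statement about the power of the trial as it will be analysed. The point is a reporting error in the trial's central justification, cheap to correct, and not a reason to doubt the target.

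**What to change.** Keep the target of about 110 and make the paragraph consistent by one of two routes, without mixing them.

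- **(a) Keep 21, 46, 92 and 110.** Restate the power as about 88% to 90% at an effect of 1.0 under the design-effect calculation, or as 80% at an effect of about 0.9, whichever was actually used. Name the formula or test.
- **(b) Keep 80% power and an effect of 1.0.** State 17 per group, 38 after the design effect, 76 in total and about 90 after 15% dropout, and say that the planned 110 exceeds this requirement.

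In either case, call the clustered figure (46 or 38) the required or inflated size. The effective size is that figure divided by 2.2: 46 / 2.2 = 20.9 or 38 / 2.2 = 17.3. Do not use the surplus under route (b) to reduce recruitment.

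The cost is a few words in one paragraph, with no change to recruitment, design or analysis.

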### Statistical analysis

2.8

All analyses will follow the intention-to-treat principle, with all children analyzed according to their randomized class regardless of adherence or attendance. Descriptive statistics will be reported for baseline demographic and developmental characteristics, including age, sex, height, weight, and baseline TGMD-3 scores, to assess comparability between groups. Continuous variables will be summarized using means and standard deviations, while categorical variables will be summarized using frequencies and percentages.

For the primary outcome of gross motor competence, linear mixed-effects models will be used to examine group (intervention vs. control) by time (baseline vs. post-intervention) interactions, accounting for clustering at the class level. Models will include random intercepts for class and child, and fixed effects for group, time, and the group-by-time interaction. Relevant covariates, including age and sex, will be included where appropriate. Because the number of clusters (classes) in the present study is relatively small, degrees of freedom for fixed effects will be estimated using the Satterthwaite approximation within the linear mixed-effects modeling framework. This approach reduces potential underestimation of standard errors and helps control Type-I error rates in studies with limited cluster numbers.

For EEG outcomes, analyses will follow the pre-specified hierarchy of neural endpoints. The primary EEG analysis will focus on frontal theta power during resting state. A secondary task-related neural index will be the N2 amplitude elicited during the Go/No-Go task. Separate linear mixed-effects models will be constructed for each neural endpoint to evaluate group-by-time interactions, using the same clustering structure as described for the primary motor outcome (random intercepts for class and child).

Additional EEG measures will include spectral power indices in the alpha and beta frequency bands, which will be analyzed using similar mixed-effects models. To account for multiple comparisons across these secondary neural measures, false discovery rate adjustments will be applied. These analyses will be interpreted as supportive and contextual rather than confirmatory.

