Several limitations warrant consideration. First, although portable EEG enables assessment in preschool environments, recordings are inherently vulnerable to movement artifacts and compliance challenges. Despite standardized preprocessing and artifact rejection procedures, some data loss is anticipated. Second, while the study is powered to detect large effects on the primary behavioral outcome, it is not powered for definitive inference regarding neurophysiological endpoints. Accordingly, EEG analyses should be interpreted as exploratory and hypothesis-generating. Third, the intervention duration is limited to one academic semester within a single regional context, and longer-term developmental trajectories cannot be inferred from the present protocol.

Despite these limitations, this study has the potential to make several important contributions. It will provide one of the first randomized controlled trials to integrate EEG into the evaluation of early motor-focused physical education, thereby linking behavioral and neural outcomes in a developmental framework. It will also generate practical insights for educators and policymakers by identifying not only whether motor-focused programs are beneficial, but also how they exert their influence on the developing brain. Ultimately, this knowledge may inform the design of optimized physical education curricula that promote both motor competence and cognitive readiness in young children, with long-term implications for academic achievement, physical activity participation, and health across the lifespan.

Within these boundaries, the study aims to contribute incremental evidence to the growing literature linking motor development and neurocognitive functioning in early childhood. The findings are intended to clarify whether structured motor-focused programs are associated with concurrent functional neural indicators during a sensitive developmental period. If such associations are observed, they may inform future research examining scalable approaches to support early developmental trajectories within educational settings.

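### The 80% power claim leaves out the number of randomised classes; on the plan's own inputs an unadjusted class-level test has about 44% power with four classes and 78% with six

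*Protocol article*

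**What the plan says.** The Sample size section reads "we adopted an assumption of an effect size of 1.0 for between-group differences", with two-sided alpha 0.05 and 80% power, and states that "an individually randomized design would require approximately 21 children per group". It assumes an average class size of 25 and an ICC of 0.05, obtains a design effect of 2.2, and arrives at 46 per group or 92 in total. Allowing for 15% dropout, "we plan to recruit approximately 110 children overall, distributed across four to six kindergarten classes in Changsha city".

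Randomization and blinding assigns whole classes 1:1. Statistical analysis plans a mixed model for group by time with random intercepts for class and child. It adds, "Because the number of clusters (classes) in the present study is relatively small", that Satterthwaite degrees of freedom will be used. The Discussion describes power in these terms: "while the study is powered to detect large effects on the primary behavioral outcome".

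**The concern.** A design effect corrects the variance of the group difference for clustering. It does not correct the degrees of freedom. With classes randomised, the group difference has to be judged against variation between classes, and k classes in two arms leave k − 2 degrees of freedom for that. With four to six classes this is 2 to 4, so the critical value is far above 1.96. Power then depends heavily on a number the plan leaves open, and one 80% claim covers designs of very different strength.

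The four-class case is not remote. At 25 children per class, 92/25 = 3.7 and 110/25 = 4.4, so the design effect of 2.2 describes roughly a four-class trial. The number of classes has to be settled before randomisation and cannot be repaired in the analysis. If it is four, a valid test that shows no difference could be misread as evidence of no benefit from a trial described as adequately powered.

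**Working it through.** **Inputs (Sample size section).** d = 1.0 with SD = 1; two-sided alpha 0.05; power 80%; 21 per group before clustering; class size 25; ICC 0.05; 92 analysed; about 110 recruited; four to six classes.

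**The plan's own chain**
- n per group for individual randomisation: 2 × (1.96 + 0.84)² / 1.0² = 15.7, so 16. The t-test version gives 16.7, so 17. The stated 21 does not reproduce; with 21 per group power would be about 89% (t) to 90% (normal).
- From 21 onward it does reproduce: design effect 1 + (25 − 1) × 0.05 = 2.2; 21 × 2.2 = 46.2 per group; 92 / 0.85 = 108.2, against about 110.

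**Class-level power.** With k1 and k2 classes per arm, k = k1 + k2 and m = N/k children per class:
- DE = 1 + (m − 1) × 0.05
- SE = √[DE/(k1·m) + DE/(k2·m)]
- Power comes from the noncentral t distribution with k − 2 df and noncentrality 1.0/SE.

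| Classes | N | m | DE | SE | df | critical t | power |
|---|---|---|---|---|---|---|---|
| 4 (2 v 2) | 92 | 23.0 | 2.10 | 0.302 | 2 | 4.30 | 44.3% |
| 4 (2 v 2) | 110 | 27.5 | 2.33 | 0.291 | 2 | 4.30 | 46.6% |
| 5 (2 v 3) | 92 | 18.4 | 1.87 | 0.291 | 3 | 3.18 | 63.7% |
| 5 (2 v 3) | 110 | 22.0 | 2.05 | 0.279 | 3 | 3.18 | 67.1% |
| 6 (3 v 3) | 92 | 15.3 | 1.72 | 0.273 | 4 | 2.78 | 78.0% |
| 6 (3 v 3) | 110 | 18.3 | 1.87 | 0.261 | 4 | 2.78 | 81.5% |

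Simulation (200,000 replicates per setting) gave 44.3% and 46.5% for four classes and 77.9% and 81.6% for six, with type I error about 5%. With the normal critical value of 1.96, four classes would appear to have 91–93% power, so the loss comes from the degrees of freedom and not from the design effect.

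**Sensitivity** (each range is N = 92 to 110)
- ICC 0: four classes 69–75%. ICC 0.01: four 62–67%, six 91–94%. ICC 0.10: four 33–34%, six 64–67%.
- Six classes, ICC 0.05: d = 0.8 gives 60–64%; d = 0.5 gives 29–31%.
- Baseline adjustment. The correlation r is my assumption, because the protocol gives none. Scaling the variance by 1 − r² at both levels, with df unchanged: four classes 53–56% at r = 0.5 and 67–69% at r = 0.7; five classes 75–78% and 88–90%; six classes 88–90% and 96–97%.

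**The planned model.** With random intercepts for class and child only, both intercepts cancel from a child's change score. The group-by-time test can then run on about N − 2 df (90 to 108). If change itself clusters by class at ICC 0.05, testing child-level change this way gave a simulated type I error of 18–20% with four classes and 13–15% with six.

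**The case against.** The strongest objection is that the table does not give the power of the analysis as written. The planned group-by-time test may use near child-level degrees of freedom, and its nominal power would then be higher. This stands, and it limits the conclusion. A reader might infer that the trial as planned will more likely than not miss the effect it is sized for. The documents do not support that: if change clusters by class, the main hazard of the model as written is a false positive. Nor does the model rescue the 80%, since power gained through an inflated type I error is not valid power. Planning Satterthwaite degrees of freedom does not settle the matter either. If they come out at class level, the table applies; if they come out near child level, the error rate is not protected.

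The second objection is that the outcome is also measured at baseline, so the unadjusted figures are pessimistic. This stands in part. Four classes stay below 80% throughout the assumed range of r, and also at ICC 0 without adjustment. Five classes could pass 80% at r near 0.7, but five cannot be split 1:1.

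Third, six classes do not quite reach the target: 78% at the planned 92, passing 80% only if nearly all 110 are analysed. This also stands. Six classes leave no reserve unless baseline adjustment supplies one.

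A reader might also see a contradiction over the source behind the effect size. The Introduction calls its meta-analytic evidence moderate to large, while the Sample size section says that trials and meta-analyses "have consistently reported large effect sizes, often exceeding 1.0". The second sentence covers a wider body of evidence and the source is not at hand, so this is a difference in emphasis and not a demonstrated contradiction.

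**Conclusion.** The concern holds in this form. The 80% figure comes from a calculation in which the number of randomised classes plays no part. Under d = 1.0, ICC 0.05 and no baseline adjustment, a valid class-level test at 92 analysed has 44% power with four classes, 64% with five and 78% with six. The power claim and the matching Discussion sentence therefore fail at four classes, and at five on the stated inputs. At six they are approximately right, with no margin.

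The plan does not ignore clustering altogether: it applies a design effect and recognises the small number of classes in the analysis section. The gap is that this recognition never reaches the sample size. The figure of 21 per group is a separate error in the cautious direction. Its surplus is already contained in the figures above and does not rescue the four-class design.

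**What to change.** 1. Set the design at six classes, three per arm with about 18 consented children each (110/6 = 18.3). Restate the class-size and design-effect inputs to match; the present 25 per class would imply 150 children in six classes. If four or five classes are kept as options, state their power of about 45% and 65%.
2. Restate power from a class-level calculation at 92 analysed: about 78% for d = 1.0, 60% for d = 0.8 and 29% for d = 0.5, conditional on ICC 0.05 and no baseline adjustment. If adjustment is to be credited, state the assumed correlation.
3. Test the group effect against between-class variation in change, through a class-by-time random effect or a class-level analysis of change or baseline-adjusted scores, so that the stated power describes the analysis. A class-level permutation test would not serve: with six classes its smallest two-sided p-value is 2/20 = 0.10.
4. Correct 21 per group to 16–17, or state the power to which 21 corresponds, and amend the Discussion sentence on power.

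The cost is a less favourable stated power, plus teacher training, fidelity visits and heart-rate monitoring for up to two more classes (at five wearers per class, up to ten more children monitored). All of this lies within the planned range of classes and needs no additional recruitment.

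### The 80% power in section 2.3 ignores the number of classes: a valid class-level test has about 44% power with four classes, 64% with five and 78% with six

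*Protocol article*

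**What the plan says.** Section 2.3 sets the planning values: "Using a two-tailed alpha of 0.05 and a statistical power of 80" percent, and "we adopted an assumption of an effect size of 1.0 for between-group differences". From these it states that "an individually randomized design would require approximately 21 children per group". It then allows for clustering: "Assuming an average class size of 25 and an intra-class correlation coefficient of 0.05, the design effect is estimated at 2.2". The outcome is given as follows: "This adjustment results in an effective sample size of 46 children per group, or 92 children in total". After a 15% dropout allowance, "we plan to recruit approximately 110 children overall, distributed across four to six kindergarten classes in Changsha city".

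Section 2.4 randomizes classes 1:1. Section 2.8 acknowledges that there are few classes and says that "degrees of freedom for fixed effects will be estimated using the Satterthwaite approximation", in a model with random intercepts for class and child. The limitations paragraph of the Discussion then says "while the study is powered to detect large effects on the primary behavioral outcome".

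**The concern.** A design effect corrects the variance for clustering. It does not change the critical value, which stays near 2, as for a test with many degrees of freedom. When whole classes are randomized, the evidence about the group difference comes from the spread between class means, and four to six means give only 2 to 4 degrees of freedom. The critical value is then 4.30, 3.18 or 2.78.

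As a result, one power figure covers layouts whose power differs widely. With four classes, which the protocol permits, a true 1.0 SD effect would be missed more often than found, while the article says the trial is powered for large effects. The number of classes cannot be changed after randomization.

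**Working it through.** **Inputs (section 2.3).** d = 1.0, two-sided alpha 0.05, ICC 0.05, class size 25, 92 children after clustering, about 110 recruited, four to six classes.

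**The plan's own chain.**
- Design effect: 1 + (25 − 1) × 0.05 = 2.2.
- 21 × 2.2 = 46.2, taken as 46 per group, 92 in total.
- 92 / 0.85 ≈ 109, or about 110.

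Everything from 21 onward reproduces. The 21 itself does not follow from 80% power: d = 1.0 needs 16 per group (normal) or 17 (t), and 21 gives 88.5% (t). That is a separate matter. It adds margin here, and the shortfall below remains despite it.

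**Class-level power.** With k classes split k₁ and k₂ and m = 92/k children per class:
- DE = 1 + (m − 1) × 0.05
- SE = √[DE × (1/(k₁m) + 1/(k₂m))]
- noncentrality = 1.0 / SE, referred to t on k − 2 df.

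| Classes | m | DE | SE | Noncentrality | df | Critical t | Power | Large-df power |
|---|---|---|---|---|---|---|---|---|
| 4 (2 v 2) | 23.0 | 2.10 | 0.302 | 3.31 | 2 | 4.30 | 44.3% | 91% |
| 5 (2 v 3) | 18.4 | 1.87 | 0.291 | 3.44 | 3 | 3.18 | 63.7% | 93% |
| 6 (3 v 3) | 15.3 | 1.72 | 0.273 | 3.66 | 4 | 2.78 | 78.0% | 96% |

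The last two columns use the same variance, so the gap between them is due to the degrees of freedom alone. The effect detectable with 80% power is 1.71 SD with four classes and 1.03 SD with six.

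**Other readings of the plan's inputs.** The stated inputs do not fix class size: 110 children in four to six classes is 27.5 down to 18.3 per class, against a stated average of 25.

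| Reading | 4 classes | 5 classes | 6 classes |
|---|---|---|---|
| DE held at 2.2, 92 analysed | 42.9% | 57.4% | 68.1% |
| All 110 analysed | 46.6% | 67.1% | 81.5% |
| 25 analysed per class (100, 125, 150 children) | 45.4% | 69.4% | 86.4% |

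The five- and six-class entries in the last row need more children than the 110 planned.

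**Other ICCs (assumed; 92 analysed).**
- 0.02: 56%, 76% and 88% with four, five and six classes.
- 0.10: 33%, 49% and 64%.

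**Baseline adjustment.** The protocol gives no baseline–post correlation, so r = 0.5 to 0.7 at both levels is an assumption. A change-score contrast multiplies the variance by 2(1 − r), and ANCOVA by 1 − r².

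| Method | 4 classes | 5 classes | 6 classes |
|---|---|---|---|
| Change score | 44–61% | 64–83% | 78–93% |
| ANCOVA | 53–67% | 75–88% | 88–96% |

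**The case against.** The strongest objection is that these figures are not the power of the model in section 2.8. They describe a post-intervention comparison of class means. The planned model tests group by time with random intercepts for class and child. With complete data both intercepts cancel from that contrast, so Satterthwaite would return child-level degrees of freedom, about 90 (92 children minus 2).

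This stands, and it rules out a stronger reading. A reader might infer that section 2.8 commits the analysis to 2–4 degrees of freedom and so contradicts section 2.3. The model as written does not do that. Nor does it rescue the stated power. Its extra degrees of freedom come from assuming that classes do not differ in their change over time, although each class is taught as a unit by its own teacher. The small-cluster protection that section 2.8 describes would then not be delivered.

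Three further objections stand in part:
- Six classes come close to 80%, and depending on the reading lie on either side of it. A reader might infer that the whole design is underpowered, but the figures do not support that at six classes.
- Five classes cannot be split 1:1, so the 64% rests on a 2-versus-3 allocation that the protocol does not describe.
- Adjusting for baseline could lift five or six classes above 80%, but section 2.3 claims no such gain, and four classes stay at or below 67% even at r = 0.7.

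**Conclusion.** The power statement is wrong as written, because it is given without regard to the number of classes. For a valid class-level test at d = 1.0 and ICC 0.05, without baseline adjustment, power is about 44% with four classes (43–47% across readings), 64% with five (57–69%) and 78% with six (68–86%, the top value needing 150 children).

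The four-class shortfall holds under every assumption tried. The five-class shortfall holds on all readings of the plan's inputs, but depends on the ICC and on taking no credit for baseline adjustment. At six classes the claim is approximately right.

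**What to change.** - **Section 2.3:** replace the single 80% with power from the noncentral t on (classes − 2) degrees of freedom for each permitted number of classes. State the class size, ICC and number analysed. Give any baseline-adjustment gain as a separate assumption, naming the method (change score or ANCOVA) and the correlation. If five classes remain possible, state how they would be split.
- **Discussion, limitations paragraph:** make the statement that the study is powered for large effects conditional on the number of classes.
- **Design:** where feasible, place the same 110 children in six classes, and settle this before randomization.

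The cost is a less favourable stated power. If six classes are used, teacher training, fidelity observation and heart-rate monitoring must also cover more classes, within the range already planned. No extra children are needed.
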